#### Pathogen detection in environmental matrices

Molecular detection of selected pathogens and faecal source tracking (FST) markers is performed for environmental samples from both the private (compound and household) and public domains using a second custom TAC.^49 56 79 80^ A subset of the enteric pathogens assessed in stool is included on the environmental TAC (adenovirus 40/41, astrovirus, norovirus GI/GII, rotavirus, sapovirus; *Aeromonas* spp, *C. jejuni*/*coli, C. difficile, E. coli* O157, EAEC; EPEC, ETEC, STEC, EIEC/*Shigella* spp, *H. pylori, S. enterica, V. cholerae, Cryptosporidium* spp, *E. histolytica, Giardia* spp, *A. lumbricoides, A. duodenale, N. americanus, T. trichiura*), as well as select environmental and zoonotic pathogens (*Leptospira* spp, *Toxocara* spp),^53 81 82^ other human pathogens detectable in faeces (SARS-CoV-2, Zika virus, HIV proviral DNA, *Plasmodium* spp, *Mycobacterium tuberculosis*),^83–86^ FST markers (human, poultry, and canine mitochondrial DNA; avian 16S rRNA),^87 88^ and general bacterial and anthropogenic pollution/antimicrobial resistance markers (bacterial 16S rRNA, class 1 integron-integrase gene *intl1*).^89 90^ We also culture faecal indicator bacteria (total coliforms and *E. coli*) using the IDEXX Colilert-18 and Quanti-Tray 2000 system.^88 91^ We conduct ongoing genomic surveillance of SARS-CoV-2 viral lineages in wastewater samples using amplicon-based Illumina next generation sequencing.^92^

### Statistical analysis

#### Enteric pathogen outcomes

We will use mixed effects models with varying slopes and intercepts to simultaneously estimate individual treatment effects for each pathogen and the weighted-average intervention effect across all pathogens included in the model. The modelling approach, including illustrative model specifications for both binary and continuous outcomes and interpretation of model parameters, is described in the prespecified data analysis plan (https://osf.io/e7pvk/). Briefly, the observed value (detection or gene copy density) of each pathogen for every child will be included as a separate response in the model design matrix and the intercept, intervention effect slope, and the slopes of other covariates will all be allowed to vary by pathogen. The intercept will also vary by child and compound to account for repeated measures of multiple pathogens per child and multiple children per compound. Each set of pathogen-varying effects (eg, the pathogen-specific intervention effect slopes) will be structured as arising from a population of parameters with shared mean and variance,^93 94^ where the population-level mean corresponds to the weighted-average expected effect across all pathogens and the population-level variance indicates the extent to which the effect may differ by pathogen. We will also estimate covariances between the sets of pathogen-varying effects to account for dependencies, for example, if the effect of the intervention on a specific pathogen is greater when the background prevalence of that pathogen (represented by the pathogen-specific intercept) is also higher. By partially pooling information between pathogens, this approach provides adaptive shrinkage of the individual treatment effect estimates for each pathogen as well as an estimate of the generalised effect across pathogens.^50 93^ Such partial pooling of effect estimates helps control the false discovery rate for individual outcomes, mitigating the need for post hoc multiple comparison adjustments.^69 70^ As a sensitivity analysis, we will also fit separate models for each pathogen, applying the Benjamini-Hochberg procedure to control the false discovery rate.^95^

The mixed effects models will be specified as Bayesian hierarchical models with regularising hyperpriors (see data analysis plan for discussion of prior distributions) and sampled using Markov chain Monte Carlo approaches.^50 93 96^ For binary enteric pathogen detection outcomes, the canonical logistic link function will be used for computational stability and a Bayesian parametric g-formula algorithm will be applied to estimate marginal prevalence ratios (PR) and differences (PD) from the posterior predictive distribution.^97^ Posterior predicted probabilities will be sampled for each pathogen assuming all participants received the intervention and again assuming none received the intervention, leaving all other covariate values unchanged, to obtain weighted averages over the distribution of confounders in the sample population, as in marginal standardisation.^98^ The posterior predicted PR and PD distributions for each pathogen will be approximated by the ratio and difference, respectively, of the posterior predicted probability draws under the all-treated and none-treated scenarios. Differences in average gene copy density (scaled by pathogen-specific sample standard deviation to facilitate comparison across pathogens) will be estimated as the measure of effect using linear Bayesian hierarchical models for semicontinuous enteric pathogen quantity outcomes, with non-detects considered true zeros and censoring used to create a zero class (as in Tobit regression; refer to data analysis plan for implementation details).^96 99^ As a sensitivity analysis, we will also implement the two-stage parametric g-formula approach of Rogawski McQuade *et al* to estimate differences in average quantity separately for each pathogen, applying the Benjamini-Hochberg procedure to account for multiple comparisons.^11^ Effect estimates will be summarised using the mean of the posterior predictive distribution to represent the expected effect size and the central 95% probability interval to describe the range of effect sizes compatible with the data (the 95% CI). Parameters with 95% CIs that exclude the null will be considered significant, although the magnitude and uncertainty of parameter estimates will also be considered holistically in evaluating evidence for clinically meaningful effects.^100^

#### Growth and caregiver-reported outcomes

The effects of the intervention on mean HAZ, WAZ, and WHZ; the prevalence of stunting, underweight, and wasting; and the period-prevalence of caregiver-reported diarrhoea and negative control outcomes (bruising, scrapes, and abrasions; toothache) will be analysed separately as secondary outcomes using generalised estimating equations and robust standard errors with exchangeable correlation structure and clustering by compound (the level at which the sanitation intervention was delivered).^13 34 101^ The estimated difference in age-adjusted z-scores by treatment assignment will be used as the measure of effect for continuous anthropometry outcomes. The PR will be estimated by modified Poisson regression for binary growth status and caregiver-reported outcomes. We will not adjust for multiple comparisons.^31 102^

#### Covariates and effect measure modification

As a cross-sectional study of an existing intervention, all analyses will be adjusted for a set of covariates selected a priori as potential confounders of the sanitation-enteric pathogen shedding relationship.^103^ The adjustment set will include child age and sex, caregiver’s education, and household wealth index; additional covariates will be considered in exploratory adjusted analyses.^10 11 34 104^ Records missing covariate data will be excluded from primary analyses. Analyses will be repeated with missing data imputed by multivariate imputation using chained equations (MICE) as a sensitivity analysis.^34 105^ In addition to covariates, caregiver-reported outcomes and continuous growth outcomes (HAZ, WAZ, and WHZ) will be used for imputation; derived binary growth statuses (stunting, underweight, and wasting) will be recalculated for each observation after conducting imputation procedures. Missing pathogen outcomes will not be imputed, nor will pathogens be used to inform imputation of other variables. However, datasets containing imputed covariates will be joined to observed pathogen outcomes by unique child identifier for sensitivity analyses; the Bayesian hierarchical models will be fit to each imputed dataset and draws from the posterior predictive distributions for parameters and contrasts of interest will be concatenated to obtain pooled estimates across the multiple imputed datasets.^106^ The specific enteric pathogens detected are expected to be strongly related to child age.^8 34^ We will examine effect measure modification of the primary and secondary outcomes stratifying by age group (1–11 months, 12–23 months, and 24–60 months).^3 107^

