## Methods and analysis

### Study setting

This household-based study is being conducted in 11 bairros (neighbourhoods) in the Nhlamankulu district and 5 bairros in the KaMaxaquene district of Maputo city, Mozambique. Households in these densely populated, low-income neighbourhoods typically cluster into self-defined compounds delineated by a wall or boundary that share outdoor living space and sanitation facilities. Study activities with participating households are conducted primarily in the compound shared outdoor space by staff from the Centro de Investigação e Treino em Saúde da Polana Caniço (Polana Caniço Health Research and Training Centre; CISPOC) in Maputo, Mozambique, from which the study is implemented and managed.

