### Study design

#### Urban sanitation intervention

The non-governmental organisation (NGO) water and sanitation for the urban poor (WSUP) implemented a sanitation intervention in 2015–2016 at approximately 300 compounds in informal urban neighbourhoods of Maputo under a larger programme led by the Water and Sanitation Programme of the World Bank.^47^ In these compounds, ranging between three and 25 households each, existing shared, unhygienic latrines were replaced with pour-flush toilets and a septic tank with a soak-away pit for the liquid effluent. Two intervention designs employing the same sanitation technology were implemented, with approximately 50 communal sanitation blocks (CSBs) and 250 shared latrines (SLs) constructed across 11 neighbourhoods that exhibited diversity across density and other key characteristics (susceptibility to flooding, relative poverty, access to water and sanitation infrastructure).^12 52 54^ SLs served compounds with fewer than 21 residents and provided a single cabin with the intervention toilet, while CSBs provided an additional cabin for every 20 compound residents and other amenities including rainwater harvesting, municipal water connections and storage, and washing, bathing and laundry facilities.^34 55^ WSUP also constructed facilities to the same specifications at other compounds in the neighbourhoods prior to 2015 and continued to deliver these intervention designs in the years following 2016.

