#### Original controlled before-and-after study

To evaluate the impact of the WSUP sanitation intervention on child health, we conducted the Maputo Sanitation (MapSan) trial, a controlled before-and-after study of enteric pathogen detection in child stool (ClinicalTrials.gov: NCT02362932).^47^ WSUP selected intervention compounds using the following criteria: (1) residents shared sanitation in poor condition as determined by an engineer; (2) the compound was located in the predefined implementation neighbourhoods; (3) there were no fewer than 12 residents; (4) residents were willing to contribute financially to construction costs; (5) sufficient space was available for construction of the new facility; (6) the compound was accessible for transportation of construction materials and tank-emptying activities; (7) the compound had access to a legal piped water supply and (8) the groundwater level was deep enough for construction of a septic tank. Control compounds were selected according to criteria 1, 3, 4 and 7 from the 11 neighbourhoods where the intervention was implemented and 5 additional neighbourhoods with comparable characteristics.^12^

The MapSan trial recruited an open cohort at three time points: baseline (preintervention), 12 months postintervention, and 24 months postintervention; children were eligible to participate if older than 1 month at the time of enrolment and under 48 months at baseline. We enrolled intervention and control compounds concurrently to limit any differential effects of seasonality or other secular trends on the outcomes. We found no evidence that the sanitation intervention reduced the combined prevalence of 12 bacterial and protozoan enteric pathogens (the prespecified primary outcome), the individual prevalence of any single bacterial, protozoan, soil-transmitted helminth (STH), or viral pathogen, or the period prevalence of caregiver-reported diarrhoea 12 and 24 months postintervention.^34^ However, exploratory analyses indicated the intervention may have been protective against bacterial and STH infections among the cohort who were born into the intervention and may have reduced the spread of some pathogens into latrine entrance soils.

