### Limitations

As an observational, cross-sectional evaluation of an existing intervention, this study faces a number of limitations that may impact the generalisability of our findings. By design, all of the study participants will have been born after the intervention was implemented in order to evaluate intervention impacts among individuals across a range of ages who have been exposed to intervention for their entire lives. However, there is potential for confounding bias in our estimates of the intervention impacts on child health, particularly concerning socioeconomic factors that may be associated with increased pathogen exposures. While non-randomised, the criteria for intervention and control compounds differed only by engineering considerations that we believe to be independent of the outcome. However, in the years since the intervention was implemented, the presence of the intervention itself may have influenced the desirability of the intervention sites and thus the socioeconomic status (SES) of their residents, particularly in light of the high population turnover previously observed after only 1–2 years. All analyses will be adjusted for a location-specific wealth index to account for potential differential SES between treatment arms,^104^ in addition to other prespecified covariates associated with enteric pathogen exposure that may plausibly be related to treatment status, but the possibility of unmeasured and insufficiently controlled confounding remains.

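### Controls come partly from five neighbourhoods outside the intervention area, but the prespecified analyses have no neighbourhood or district term, and the Limitations section omits location as a difference between the arms

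*Protocol article*

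**What the plan says.** **Where the arms come from.** Under Urban sanitation intervention, the facilities were "constructed across 11 neighbourhoods that exhibited diversity across density and other key characteristics"; the characteristics listed are "susceptibility to flooding, relative poverty, access to water and sanitation infrastructure". Under Original controlled before-and-after study, one of the eight selection criteria for intervention compounds reads "2) the compound was located in the predefined implementation neighbourhoods". Controls had to meet only criteria 1, 3, 4 and 7, and were taken "from the 11 neighbourhoods where the intervention was implemented and 5 additional neighbourhoods with comparable characteristics". Study setting places the follow-up in "11 bairros (neighbourhoods) in the Nhlamankulu district and 5 bairros in the KaMaxaquene district".

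**How the arms are compared.** Covariates and effect measure modification fixes the adjustment set as child age, sex, caregiver education and "household wealth index; additional covariates will be considered in exploratory adjusted analyses". Under Enteric pathogen outcomes, the primary model has effects that vary by pathogen and intercepts that also vary by child and compound. Under Growth and caregiver-reported outcomes, the GEE models cluster by compound.

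**How comparability is defended.** Limitations states that "the criteria for intervention and control compounds differed only by engineering considerations that we believe to be independent of the outcome".

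**The concern.** Area is tied to arm by the way compounds were selected: the intervention went to 11 neighbourhoods, and some controls lie outside them. The original study was a controlled before-and-after comparison, which can remove stable differences between areas. The follow-up is a single cross-sectional survey and cannot, so the adjustment has to do that work.

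The prespecified adjustment has no area component. A compound-level intercept models correlation among children in the same compound; it does not remove confounding by the area in which the compound lies. The g-formula step standardises over the modelled covariates only, so the marginal prevalence ratio inherits the omission. Wealth and caregiver education are socioeconomic measures and may capture little of area features such as flooding or density.

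At stake is whether part of the estimated effect, in either direction, reflects where controls live rather than the sanitation they use. The sentence in Limitations hides the question, because it tells the reader that the arms' criteria differed in engineering terms alone.

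**Working it through.** **1. Compare the selection criteria with the Limitations sentence.** Controls met criteria 1, 3, 4 and 7, so criteria 2, 5, 6 and 8 applied to intervention compounds only. Criteria 5 (space for construction), 6 (access for materials and emptying) and 8 (groundwater depth for a septic tank) are engineering matters. Criterion 2 is location. The Limitations sentence is therefore incorrect on one criterion of four, and that one defines the area difference.

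**2. Bias when there is no true effect.** Let f be the share of control children living in the 5 additional neighbourhoods and r the background prevalence there relative to the 11. The documents give neither, so both are assumptions. If prevalence is p in the 11 areas, the intervention arm has p and the control arm has p(1 - f) + p·f·r. Hence

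apparent PR = 1/(1 - f + f·r).

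| f | r | Denominator | Apparent PR |
|---|---|---|---|
| 0.25 | 1.2 | 1.05 | 0.95 |
| 0.50 | 1.2 | 1.10 | 0.91 |
| 0.20 | 0.8 | 0.96 | 1.04 |
| 0.40 | 0.8 | 0.92 | 1.09 |
| any | 1.0 | 1.00 | 1.00 |

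These values are crude, before wealth and education absorb any of the difference.

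**3. Reproduce the plan's detectable effect, so that the fix can be costed.** Inputs from Minimum detectable effect size: 80% power, 5% significance (taken as two-sided), compound cluster variance 0.05; 200 compounds per arm with 2 children each (conservative) or 300 with 2.5 (maximal). With cC and cT compounds per arm and m children per compound,

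Var(difference) = [pC(1 - pC)/m + 0.05]/cC + [pT(1 - pT)/m + 0.05]/cT.

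Solving for the baseline prevalence at which a 25% reduction has 80% power gives 46.0% (conservative; the plan states 46%) and 33.2% (maximal; the plan states 34%). The plan's figures are reproduced closely enough to use the formula.

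**4. Cost of restricting to the 11 shared neighbourhoods.** Keep 200 intervention compounds and 200(1 - f) control compounds, assuming the same number of children per compound everywhere. In the conservative scenario take pC = 0.46, pT = 0.345 and m = 2. The control term is 0.1242 + 0.05 = 0.1742 per compound and the intervention term is 0.1130 + 0.05 = 0.1630.

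- f = 0: variance 0.1742/200 + 0.1630/200 = 0.001686, SE 0.0411, 0.115/0.0411 = 2.80, power 80%.
- f = 0.2: variance 0.1742/160 + 0.1630/200 = 0.001904, SE 0.0436, ratio 2.64, power 75%.
- f = 0.5: variance 0.1742/100 + 0.1630/200 = 0.002557, SE 0.0506, ratio 2.27, power 62%.

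Intermediate values are 72% at f = 0.3 and 68% at f = 0.4.

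**The case against.** The protocol describes the 5 additional neighbourhoods as comparable, and its list of varying characteristics concerns diversity among the 11, not a contrast between the 11 and the 5. Both arms had to have shared sanitation in poor condition and legal piped water at selection, and the wealth index addresses relative poverty. Limitations admits possible residual confounding, and additional covariates may enter exploratory models. The separate data analysis plan is not shown and may contain area analyses. All of this stands, and it limits the likely size of the problem. It does not remove it: no data support the statement of comparability, the confounding discussion centres on socioeconomic status, and the article itself fixes the main adjustment set without area.

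A reader might infer more than the documents support:

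- *That area differences pass in full into the effect.* They do not. Controls also come from the 11 shared neighbourhoods, so only the share f carries the difference, less what the covariates absorb.
- *That the bias favours the intervention.* With r below 1 it would mask a benefit.
- *That a calendar-time term is also needed.* Both arms are enrolled concurrently, which handles seasonality and secular trend by design.
- *That the intervals are too narrow.* No neighbourhood correlation is given. Where both arms share a neighbourhood its effect partly cancels, so the net direction cannot be told.
- *That the groundwater criterion also contradicts Limitations.* It is worded as a construction requirement, which is an engineering consideration.
- *That the 5 KaMaxaquene bairros are the control-only areas.* The counts match, but the text does not say so. Nor does it state how intervention compounds are distributed across neighbourhoods at follow-up.

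**Conclusion.** The point holds in a limited form. Area is associated with arm through the original selection, and neither the prespecified adjustment set nor the model levels include it. The sentence in Limitations is wrong because location also separated the arms. The resulting bias is proportional to the share of controls in the 5 additional areas and could run either way; under the assumed values above it moves a null prevalence ratio to somewhere between 0.91 and 1.09. It is zero if background prevalence is the same in both sets of areas. The documents do not allow the actual size or sign to be determined, nor whether the pooled estimate would cross the significance threshold. The change is worth making because the follow-up has no baseline to difference out stable area effects and the location of compounds is already recorded.

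**What to change.** 1. Correct the Limitations sentence to say that location in the implementation neighbourhoods, as well as engineering criteria, applied to intervention compounds only.
2. Add a neighbourhood varying intercept, also allowed to vary by pathogen, to the primary model, and an area term to the GEE models.
3. Prespecify a sensitivity analysis restricted to the 11 neighbourhoods that contain both arms.

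Reporting the number of compounds by arm and neighbourhood would let readers see f directly.

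**Cost.** No new data are needed. There is some loss of precision, and more weight falls on within-neighbourhood contrasts, where spillover between compounds could pull the estimate toward the null. A partially pooled intercept may not remove all area confounding, which is why the restricted analysis is needed beside it. Restriction is the more expensive step: conservative-scenario power at 46% prevalence falls from 80% to about 75% if 20% of controls are excluded and to about 62% if 50% are. It should therefore be a sensitivity analysis and not replace the primary one.

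### Barring pathogen results from the covariate imputation lets confounding back into the missing-data sensitivity analysis of the pathogen outcomes

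*Protocol article*

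**What the plan says.** All of the rules stand in the protocol article under Covariates and effect measure modification.

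- Adjustment set: "The adjustment set will include child age and sex, caregiver’s education, and household wealth index".
- Primary handling: "Records missing covariate data will be excluded from primary analyses".
- Check on that handling: "Analyses will be repeated with missing data imputed by multivariate imputation using chained equations (MICE) as a sensitivity analysis".
- Imputation predictors: "In addition to covariates, caregiver-reported outcomes and continuous growth outcomes (HAZ, WAZ, and WHZ) will be used for imputation".
- Pathogens: "Missing pathogen outcomes will not be imputed, nor will pathogens be used to inform imputation of other variables".
- Use of the result: "datasets containing imputed covariates will be joined to observed pathogen outcomes by unique child identifier for sensitivity analyses". The Bayesian hierarchical models are then fitted to each completed dataset and the posterior draws are concatenated.

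The article gives no reason for keeping the pathogens out and no expected fraction of records with missing covariates. Under Limitations it says that "there is potential for confounding bias in our estimates of the intervention impacts on child health, particularly concerning socioeconomic factors", and it relies on the wealth index and the other covariates to control this.

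**The concern.** An imputation model should contain the outcome of the model that will use the imputed values. If it does not, a missing wealth or education value is drawn as though unrelated to pathogen detection, given the other predictors. In those records the covariate carries too little information about the outcome, so the fitted confounder-pathogen slope shrinks and the intervention effect is under-adjusted. More imputations do not cure this, and it occurs even when values are missing completely at random.

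The plan meets the principle for growth and caregiver-reported illness, whose outcomes are in the imputation model. It departs from it only for the pathogens, which include the primary outcome. The study is non-randomised, and this is the only check that the article describes on dropping records with missing covariates. If intervention compounds have become wealthier and wealth is protective, which is the worry raised in the article, the distortion exaggerates benefit. A reader comparing the two analyses could then take an artefact of the imputation for evidence about the excluded records.

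**Working it through.** The article gives no figure on missing covariates, so it has none to reproduce on this point. Its detectable effects do reproduce. With the variance of an arm prevalence taken as [0.05 + p(1−p)/m]/k, power for a 25% reduction is 0.800 at 46% baseline (k = 200, m = 2) and 0.815 at 34% (k = 300, m = 2.5). The point does not depend on them.

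**Inputs.** From the article: the imputation predictors, the bar on pathogens, the later join, and the logistic model with marginal standardisation (Enteric pathogen outcomes). Assumed: the fraction f of records with an imputed confounder, the arm gap g in that confounder, and its slope β on the outcome.

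**Step 1, algebra.** Take one confounder, a linear model and no true effect. The crude arm difference is βg. Values imputed from arm alone have the right spread but no covariance with the outcome within arm, so the fitted slope is (1−f)β. The adjusted arm coefficient is βg − (1−f)βg = fβg, so the share of confounding left in is f. With g = 0.4 SD and β = −0.3, βg = −0.12. For f = 0.10, 0.20 and 0.30 the bias is −0.012, −0.024 and −0.036.

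**Step 2, simulation of that case** (n = 1100, 400 datasets per fraction, 5 imputations each, arm in the imputation model, truth 0):

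| Missing | Outcome excluded | Outcome included | Complete case | Excluded minus complete case | Share of 0.12 |
|---|---|---|---|---|---|
| 10% | −0.009 | 0.002 | 0.002 | −0.011 | 9% |
| 20% | −0.024 | −0.001 | 0.000 | −0.024 | 20% |
| 30% | −0.043 | −0.008 | −0.008 | −0.035 | 29% |

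The wealth slope was attenuated by 9%, 20% and 29%, in line with Step 1.

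**Step 3, closer to the plan.** Logistic model with marginal standardisation to a prevalence ratio (PR), 200,000 records per scenario, covariate missing completely at random. The confounder was imputed from arm, a height-for-age proxy and diarrhoea, without or with the pathogen result. Share = (PR without − true)/(crude − true), from unrounded values.

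| Gap, log-odds slope | Missing | True | Crude | Complete case | Without pathogen | With pathogen | Share |
|---|---|---|---|---|---|---|---|
| 0.5, −0.6 | 10% | 0.850 | 0.713 | 0.848 | 0.834 | 0.846 | 0.12 |
| 0.5, −0.6 | 20% | 0.850 | 0.717 | 0.852 | 0.824 | 0.850 | 0.20 |
| 0.5, −0.6 | 40% | 0.850 | 0.718 | 0.852 | 0.799 | 0.849 | 0.38 |
| 0.5, −0.6, null | 20% | 1.000 | 0.855 | 0.999 | 0.974 | 0.999 | 0.18 |
| 0.3, −0.4 | 20% | 0.848 | 0.793 | 0.848 | 0.839 | 0.848 | 0.17 |
| 0.3, −0.4 | 40% | 0.848 | 0.798 | 0.857 | 0.835 | 0.856 | 0.25 |

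Second row: (0.824 − 0.850)/(0.717 − 0.850) = 0.026/0.133 = 0.20. With gap 0.5 the slope of −0.60 fell to −0.48 at 20% missing and −0.38 at 40%. The weak proxies did not repair it. At 2% and 5% missing the shares ran from −0.13 to 0.11, which is simulation noise. The last row shows the size of that noise, since two unbiased methods sit 0.008 to 0.009 above the truth.

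**Step 4, missingness related to the outcome.** In the logistic model, with missingness depending on both outcome and arm:

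- Gap 0.3, 20% missing: true 0.848, complete case 0.823, planned imputation 0.833, with pathogen 0.843.
- Gap 0.5, 19% missing: true 0.850, complete case 0.823, planned imputation 0.818, with pathogen 0.841.

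In the linear model (truth 0), with missingness depending on the outcome in one arm only, complete case gave −0.118 and the planned imputation −0.007 at 12% missing, and −0.202 and −0.017 at 22%. A separate run at 12% gave −0.19 and about 0.00.

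**The case against.** Much of the case on the other side stands, and it rules out four stronger readings.

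- *The primary result is biased.* A reader might infer this because the pooled pathogen effect is the primary outcome. The article makes complete case the primary analysis and imputation a sensitivity analysis, so the primary estimate is untouched.
- *The planned check is always worse than complete case.* Step 4 refutes this. When missingness depends on the outcome in one arm only, complete case fails badly and the planned imputation would expose it. The ranking against the planned check holds where missingness is independent of the outcome given the covariates.
- *Imputed records are effectively unadjusted.* That goes too far. A record missing wealth is still adjusted for observed age, sex and education, and its wealth is drawn using growth and caregiver-reported illness.
- *Study arm is also left out of the imputation.* The predictor list does not name arm, but this is silence in a condensed article whose analysis plan is not shown. No figure that assumes arm is omitted is relied on here.

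The size is also uncertain. Questionnaires are administered in person by trained staff and age decides eligibility, so nothing in the article points to 20% or 30% missing. In the linear setting, 2% and 5% missing each gave −0.005 against a crude bias of about −0.12. With weaker confounding and 20% missing, 0.839 against 0.848 is small beside the 25% to 50% reductions discussed under Minimum detectable effect size. Both simulations use one outcome without clustering, so they show direction and proportion, not this trial's actual bias.

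The mechanism survives all of this. The bar on pathogens is a stated rule, and an unseen analysis plan could not reverse it without contradicting the article.

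**Conclusion.** The point holds for the missing-data sensitivity analysis of the pathogen outcomes, including the primary pooled effect. As written, that analysis moves toward the unadjusted estimate by a share close to the fraction of records with imputed confounders: roughly 10%, 20% and 30% of the crude bias at 10%, 20% and 30% missing, and negligible below about 5%. The missing fraction, the arm gap and the confounder slope are assumptions, as the article states none of them. The growth and caregiver-reported analyses do not share the fault. The practical harm is to interpretation: where covariates are missing independently of the outcome given the covariates, complete case is unbiased and its check is not, so disagreement between them could come from the imputation itself. It should be changed because the remedy is cheap, not because the main result is at risk.

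**What to change.** Strike the second clause of the sentence on pathogens, the one that bars them from informing other imputations. Keep the first clause, so that missing pathogen results are still not imputed. Then specify one of two routes for the pathogen analyses:

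1. Run a separate imputation among children with a stool result. Include as predictors the observed pathogen detection (for example the number of the 22 detected plus indicators for the common pathogens) and study arm, alongside the predictors already listed.
2. Impute the missing covariates jointly within the Bayesian hierarchical model.

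Keep the existing imputation for the growth and caregiver-reported outcomes. Restricting route 1 to children with a stool result matters: in a single shared run, children without one would have missing predictors.

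The cost is a second imputation run and a few more predictors. A count with indicators is also only approximately compatible with a model whose covariate slopes vary by pathogen. Route 2 avoids that approximation but needs more modelling work.
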